### Within group effects

Within the IIG there will be a significant reduction in anxiety scores on the RCADS from T1 to T2.Within the DIG there will be a significant reduction in anxiety scores on the RCADS from T2 to T3.

For the qualitative process evaluation of the programme, all ten intervention sessions will be video recorded, and the verbal content of the recordings will be transcribed verbatim. The transcriptions will be analysed to identify recurring themes (thematic content analyses). After completion of the ten sessions participants will also be asked to complete a series of short questions compiled by the researcher. In addition, the researcher and the research assistant (observer) will also keep a detailed record (in the form of process notes) of all sessions. The intervention programme will be completely manualised and a quantifiable measure, to measure adherence to the treatment protocol, will be developed and implemented. These qualitative components will be included in the research to ensure fidelity and to provide as many pointers as possible to aid in the understanding of an under-researched problem, namely anxiety experienced by children with visual impairments.

Hartley and Muhit (2003) state that the inclusion of a qualitative component in research can help bridge the gap between scientific study and clinical practice, and may assist in gaining a better understanding of the phenomena under investigation. They further argue that qualitative methodology is needed to collect cultural and disability specific data which may not be easily obtained through quantitative methods, as the low prevalence rates of some disabilities make it very difficult to draw statistically significant conclusions from quantitative data (Philander 2007). Hartley and Muhit (2003:103) further emphasise that qualitative sources of data provide an opportunity not only to listen, but also to include the voices of vulnerable populations in programme planning. They stated this as follows: ‘it [*qualitative data*] educates quantitative researchers about the people and their perceptions, beliefs and practices’.

## Data collection

Questionnaires will be made available in four different input modes relating to the individual participant's specific needs and degree of visual impairment. In some cases the original print versions of the questionnaires will be provided and read by means of a magnifying aid, questionnaires will also be put in a large print format (A3), and for those participants who cannot read print, the questionnaires will be made available in braille or in an audio format. The modes of response will also be adapted to suit the individual participant's communication needs. Participants who are able to read the standard or large print copies of the questionnaires can indicate their answers in the spaces provided, and for the participants using braille or recorded versions of the questionnaires, specially prepared answer sheets will be made available.

In previous studies (King, Gullone & Stafford 1990; Matson *et al.*
1986; Ollendick, Matson & Helsel 1985; Wilhelm 1989) where the fears and anxieties of visually impaired children were assessed using self-report measures (e.g. The Revised Fear Survey Schedule for Children, FSSC-R; The South African Fear Survey Schedule for Children, FSSC-SA; and the Revised Children's Manifest Anxiety Scale, RCMAS) similar adaptations were made with great success. Children will complete the questionnaires at their school with the help of the research facilitators. Guidelines put forth by Visagie and Loxton (2014) about the child-friendly assessment and the accomodations needed for children with visual impairments to complete self-report surveys, will be implemented and followed throughout the process of data collection.

The questionnaires will be administered to all participants (IIG and DIG) on four occasions:

Immediately before delivering the anxiety intervention programme to the IIG (T1) (Baseline)Immediately after delivering the anxiety intervention programme to the IIG, and before delivering the anxiety intervention programme to the DIG (T2)Immediately after delivering the anxiety intervention programme to the DIG (T3)At follow-up, six months after delivering the programme to the IIG, and three months after delivering the programme to the DIG (T4)

### Participant outcomes

The primary outcome measure in the study relates to changes in levels of symptoms of anxiety and depression on the Revised Child Anxiety and Depression Scale (RCADS) (Chorpita *et al.*
2000). The 30 items of the RCADS assess symptoms across six domains of anxiety and depression in children (aged 6–18), including:

social phobiaseparation anxietyobsessive compulsive disorderpanic disordergeneralised anxiety disordermajor depressive disorder.

Items are rated on a four-point Likert scale. Psychometric properties of the RCADS are good; the six RCADS scales were found to have adequate internal consistency (with all alphas in the .70 and .80 range) and test-retest stability (with one-week test-retest correlation coefficients ranging from .65 to .80) (Chorpita *et al.*
2000; Muris, Meesters & Schouten 2002). The RCADS is freely available on the Internet for download, and permission to translate the questionnaire into Afrikaans was obtained from the authors. Translations were written by a registered clinical psychologist who is fluent in both English and Afrikaans in accordance with the Brislin (1980) back-translation method.

Secondary outcome measures relate to children's worry and self-efficacy measured by the Penn State Worry Questionnaire for Children (PSWQ-C) (Chorpita *et al.*
1997) and Self-Efficacy Questionnaire for Children (SEQ-C) (Muris 2001) respectively. The PSWQ-C (Chorpita *et al.*
1997) is an 11–item questionnaire which assesses the tendency of children (aged 7–17) to engage in excessive generalised and uncontrolled worry. Respondents are asked how often each item applies to them by indicating answer options on a four-point Likert scale. Chorpita *et al.* (1997) found the PSWQ-C to have favourable psychometric properties, reporting good internal consistency (*A* = .88) and test-retest reliability (*R* = .92) (over a one-week interval). The PSWQ-C is freely available on the Internet for download, and permission was obtained from the authors to translate the questionnaire into Afrikaans. Once again translations were written in accordance with the Brislin (1980) back-translation method. Muris’s (2001) SEQ-C is a 24 item self-report scale. The SEQ-C measures children's self-efficacy across three domains including: social, academic and emotional self-efficacy. Respondents are required to rate each of the 24 items on a five-point Likert scale. The reliability of the scale ranges from .88 for total self-efficacy and between .85 and .88 for the three sub-scales (Muris 2001). The SEQ-C has been translated into Afrikaans and has been used successfully in previous studies (Le Roux 2013; Muris 2001).

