**Method:**

A specifically tailored cognitive-behavioural therapy-based anxiety intervention, for 9–13 year old South African children with visual impairments, will be evaluated in two special schools. The study will employ a randomised wait-list control group design with pre- post- and follow-up intervention measures, with two groups each receiving a 10 session anxiety intervention programme. The main outcome measure relates to the participants’ symptoms of anxiety as indicated on the Revised Child Anxiety and Depression Scale.

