The high prevalence rates of anxiety symptomology in the general population (especially in South Africa)The suggestion that visually impaired children are at increased risk for the development of anxiety disorders when compared to their sighted counterpartsThe lack of anxiety research involving children with visual impairmentsThe unique South African socio-cultural contextThe benefits associated with prevention and early intervention with regards to childhood anxietyThe inaccessibility and appropriateness of existing anxiety intervention programmes.

As a result, the proposed study will aim to develop, implement and evaluate an anxiety prevention or early intervention programme (from here on referred to as an anxiety intervention programme), which is specifically tailored to meet the needs of children with visual impairments within the South African context. As far as the researchers can ascertain, no studies focussed on anxiety prevention and early intervention programmes, for children with visual impairments, have been conducted previously.

Thus, the primary aim of the study is to develop, implement and evaluate a specifically tailored anxiety intervention programme for use with South African children with visual impairments. This aim will unfold in the following three steps:

develop an accessible anxiety intervention programme which can be used with South African children with visual impairments (programme development phase).implement this anxiety intervention programme successfully (programme implementation phase).evaluate the effectiveness of this anxiety intervention programme in maintaining emotional health (i.e. preventing an increase in symptoms of anxiety as measured on the Revised Child Anxiety and Depression Scale [RCADS] [Chorpita *et al.*
2000] [programme evaluation phase]).

Specifically, it is expected that firstly, there will be a significant reduction in anxiety scores on the RCADS from Time 1 (T1) to Time 2 (T2) for the immediate intervention group (IIG), and secondly, there will be a significant reduction in anxiety scores on the RCADS from T2 to T3 for the delayed intervention group (DIG).

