## Discussion

This study will employ a randomised wait-list control group design with pre and post-intervention measures to evaluate the effectiveness of a specifically tailored, group-based, CBT anxiety intervention programme for 9–13 year old South African children with visual impairments. It is hypothesised that children in the IIG will experience significantly reduced symptoms of anxiety when compared to children in the DIG.

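### The primary RCADS score is named in two ways, and effectiveness is tied to within-group change although the randomised comparison is available and is never made decisive

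*Protocol article*

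**What the plan says.** **Which score.** The abstract states: "The main outcome measure relates to the participants’ symptoms of anxiety as indicated on the Revised Child Anxiety and Depression Scale". The Participant outcomes section states: "The primary outcome measure in the study relates to changes in levels of symptoms of anxiety and depression". That section also says that the RCADS items "assess symptoms across six domains of anxiety and depression in children", and the sixth domain listed is major depressive disorder. Four of the six hypotheses (the second and third between-group ones and both within-group ones) refer to anxiety scores. The first and fourth between-group hypotheses refer only to RCADS scores or results.

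**What counts as effective.** The third step of the aim, at the end of the Introduction, is to "evaluate the effectiveness of this anxiety intervention programme in maintaining emotional health (i.e. preventing an increase in symptoms of anxiety", as measured on the RCADS. The specific expectations that follow are "a significant reduction in anxiety scores on the RCADS from Time 1 (T1) to Time 2 (T2") for the IIG, and a corresponding fall from T2 to T3 for the DIG. Programme evaluation says that the immediate impact of the programme will be measured from pre and post data in each group. It also says that the DIG's T1–T2 data serve as the wait-list control for stability without treatment.

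**The randomised contrast.** The second between-group hypothesis expects lower anxiety in the IIG than in the DIG at T2. Statistical analyses compares change scores between the two groups to evaluate change due to the programme. The Discussion hypothesises that "children in the IIG will experience significantly reduced symptoms of anxiety when compared to children in the DIG". Programme evaluation lists six hypotheses, four between-group and two within-group, and no section says which of them decides effectiveness.

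**The concern.** There are two separate conflicts. First, an anxiety score and a score that includes the depression domain are different variables and can give different answers. With both published as the main or primary outcome, either can later be presented as the planned one.

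Second, the criteria for effectiveness can disagree on the same data. An unchanged score meets the no-increase criterion and fails the reduction criterion. An equal fall in both arms between T1 and T2 meets the reduction criterion for the IIG and fails the between-group criterion.

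The second conflict carries the larger risk. Self-reported symptom scores can fall on repeat completion, or with the school calendar, without any programme. The wait-list arm exists to remove such shared change. The within-group test in the IIG leaves that concurrent control (DIG, T1–T2) unused. The DIG's T2–T3 change has no untreated comparator at all, because the IIG has been treated by then. If these tests are taken as the evidence of effectiveness, shared drift counts as success.

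**Working it through.** No figure in the article depends on this point: it gives a planned sample of 60 with no alpha, power, SD or effect size. The check is therefore a comparison of criteria, followed by an illustration of size.

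**1. The criteria on three simple patterns of anxiety change, T1 to T2**

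| Pattern | No increase in IIG (aim) | Reduction within IIG | IIG better than DIG |
|---|---|---|---|
| Both groups unchanged | met | not met | not met |
| Both groups fall equally | met | met | not met |
| IIG unchanged, DIG rises | met | not met | met |

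No two columns agree throughout, so the choice of criterion can decide the conclusion.

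**2. Inputs for the illustration**
- From the article: n = 30 per group (Method); one-week test-retest correlation r = .65 to .80 for the RCADS scales (Participant outcomes).
- Assumed: no programme effect; two-sided 5% with only favourable results counted; a fall of δ = 0.2 or 0.3 SD in each interval, the same in both groups; the one-week correlation applied over about five weeks.

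**3. One within-group test**

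The SD of a change score, in units of the score SD, is √(2(1 − r)): √0.70 = 0.837 at r = .65 and √0.40 = 0.632 at r = .80. The standardised change is δ/√(2(1 − r)). The chance of a favourable paired t test (n = 30, non-central t) is:
- δ = 0.2: 0.2/0.837 = 0.239, chance 0.244; 0.2/0.632 = 0.316, chance 0.388.
- δ = 0.3: 0.3/0.837 = 0.359, chance 0.476; 0.3/0.632 = 0.474, chance 0.709.

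**4. At least one of the two within-group tests**

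The two tests use different children, so the chance is 1 − (1 − p)²:
- δ = 0.2: 1 − 0.756² = 0.428; 1 − 0.612² = 0.625.
- δ = 0.3: 1 − 0.524² = 0.725; 1 − 0.291² = 0.915.

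A simulation with Wilcoxon signed-rank tests (4,000 runs per setting) gives much the same: 0.421 and 0.605 at 0.2 SD; 0.712 and 0.905 at 0.3 SD. With no drift it gives about 0.05.

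**5. If the fall comes only at the first re-administration**

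Only the IIG's T1–T2 test is then affected, and the DIG's T2–T3 test keeps its 2.5% favourable error. At δ = 0.3: 1 − 0.524 × 0.975 = 0.489 and 1 − 0.291 × 0.975 = 0.716.

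**6. The randomised contrast**

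In the same simulation, a Mann-Whitney test on T1–T2 change between the groups is falsely favourable in 2.0% to 2.7% of runs, whatever the drift, because shared drift cancels.

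**The case against.** The strongest reply is that the valid comparison is already in the text. Statistical analyses attributes programme effect to the comparison of change scores between groups, the second between-group hypothesis and the Discussion say the same in substance, and Programme evaluation uses the untreated DIG to measure stability. This stands, and it limits the point. A reader might infer that change in either group is wholly uncontrolled. That is too strong, because the IIG's T1–T2 change has a concurrent control. What remains is that the within-group test does not use it, that the DIG's T2–T3 change has none, and that the aims name only the within-group falls.

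A second reply is that prevention and reduction suit different children: Inclusion criteria describes the programme as early intervention above a T-score of 65 and as prevention otherwise. That explains why both words appear. It does not say which result in the whole group counts as effective.

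A third reply concerns size. The drift is assumed, the higher figures need it to recur in both intervals, and the article does not state that one favourable within-group test is enough. All three are fair. If success required both within-group tests and the between-group hypothesis together, the false-positive rate could not exceed that of the between-group test. The article does not state that rule either.

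Two further inferences should be resisted. A reader might take every hypothesis to concern anxiety; the first and fourth do not name it. A reader might also quote 1 − 0.95³ = 14% as the familywise error of the three superiority hypotheses. That counts results in the unfavourable direction; counting favourable ones only, and assuming independence, it is 1 − 0.975³ = 7%. Ranking and multiplicity control are in any case commonly left to an analysis plan.

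**Conclusion.** The point holds in a limited form. The two statements of the primary score contradict each other in the current text. So do the criteria for effectiveness, in that they can give different answers on the same data. This is not detail left to a fuller document: a later plan would have to override one of the published statements.

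On the assumptions in the working, a shared decline with no programme effect produces at least one favourable within-group test in about 43% to 63% of trials at 0.2 SD per interval and about 72.5% to 91.5% at 0.3 SD. At 0.3 SD on the first re-administration only, it is about 49% to 72%. The randomised contrast stays at about 2%. These figures show how sensitive the within-group reading is; they do not predict drift in this population. The article does not say that the trial will be judged on within-group change alone, only that nothing prevents it.

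**What to change.** - In the abstract and Participant outcomes, name one primary score: the RCADS anxiety score formed from the five anxiety scales. Make the depression scale secondary.
- Make the IIG-versus-DIG comparison of T1–T2 change, already described in Statistical analyses, the single test of effectiveness. Word the second between-group hypothesis to match, since it now refers to T2 scores and not to change.
- In the aims and Programme evaluation, state effectiveness as a more favourable T1–T2 change in anxiety than in the wait-list group. This covers both prevention and reduction.
- Under Within group effects, label the IIG T1–T2 and DIG T2–T3 changes as supportive, with no claim of effectiveness resting on them.

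The cost is wording only: no added visits, measures or children. The real downside is that within-group results can no longer carry the conclusion. With 30 per group, the between-group test has about 49% power for a difference of 0.5 SD of the analysed score and 82% for 0.74 SD (normal approximation, two-sided 5% assumed). A null result would then need careful wording.

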### Teacher outcomes

An additional outcome relates to emotional and behavioural difficulties experienced by group participants. The Strengths and Difficulties Questionnaire (SDQ) is a widely used, brief behavioural screening questionnaire aimed at detecting behavioural and emotional difficulties in youth (aged 3–16 years) (Mostert 2007). The SDQ consists of 25 items which can be divided into five sub-scales of five items each. Four sub-scales comprise the most important domains of child psychopathology, including:

emotional symptomsconduct problemshyperactivity and inattentionpeer relationship problems.

Scores on these sub-scales add up to a total difficulties score. The remaining subscale (pro-social behaviour) measures the child's strengths in social interactions (Goodman 1997). Items are scored on a three-point Likert scale (Goodman *et al.*
2003). Class teachers will be asked to complete the informant version of the SDQ (Mostert 2007) on two occasions for each participant, before and directly after implementation of the anxiety intervention programme. The informant version of the SDQ assesses the teacher's perception of whether a child has a problem or not. Focus is given to chronicity, distress, social impairment and burden. The SDQ has been found to have favourable psychometric properties and the questionnaire was deemed to have good construct validity, as it was found to have substantial correlations with other indices of psychopathology (Goodman, Meltzer & Bailey 1998; Goodman, Renfrew & Mullick 2000; Goodman *et al.*
2003).

### Qualitative outcomes

The final outcome measure relates to the qualitative evaluation of the programme. It is not only important to determine whether a programme works, but also whether the participants consider the programme to be beneficial and worthwhile (Barrett & Turner 2001). For this reason, after completion of the 10 sessions, oral instructions will be given to participants to complete a series of short questions compiled by the researcher. These questions provide an opportunity to obtain qualitative feedback from the participants relating to their experience of, and satisfaction with, the anxiety intervention programme.

### Statistical analyses

The Statistical Package for the Social Sciences (SPSS) (Van Leeuwen *et al.*
2006) will be used to calculate descriptive and non-parametric statistics. As a result of the envisaged small sample size (*N* = 60), a Mann-Whitney test will be used to determine the significance of differences between the quantitative pre-and-post intervention measures (George & Mallery 2006). Pre-intervention (T1) scores will be analysed to determine the equivalence of the IIG and the DIG, before the intervention and change scores (difference between the pre-and post-intervention scores) for the IIG and DIG will be compared to evaluate change as a result of the intervention programme. Qualitative data will be analysed by means of thematic content analyses.

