## Method

A specifically tailored CBT-based anxiety intervention for South African children with visual impairments will be evaluated in two special schools that cater for children with visual impairments. This study is set up as a randomised wait-list control group design with pre-, post-and follow-up intervention measures, with 60 participants randomly assigned to an IIG (*n* = 30) and a DIG (*n* = 30). Before implementation of the programme 10 participants from each group will be randomly selected to take part in a focus group. The focus group will be aimed at obtaining the participants’ personal inputs and to pilot certain sections of the programme before final implementation. Both of the programme's groups will receive the 10 session anxiety intervention programme**.** The participants will complete baseline (T1), post intervention (T2 for IIG and T3 for DIG) and 3 month (T3 for IIG and T4 for DIG) or 6 month (T4 only for IIG) follow-up assessments.

The research design can be represented as follows:

R  IIG T1   X  IIG T2     IIG T3  IIG T4

R  DIG T1     DIG T2  X  DIG T3   DIG T4

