## Programme evaluation

As mentioned above, all assenting children from School 1 and School 2 will randomly be assigned to 1 of 2 groups at their respective school (an IIG or a DIG). The IIG groups from School 1 and School 2 will be combined to form one large IIG, whilst the DIG groups from School 1 and School 2 will be combined to form one large DIG.

The evaluation phase will comprise both a quantitative and qualitative component (more information about the qualitative component is given below). For the quantitative evaluation, all assenting children in the IIG and DIG (approximately 60 participants) will be administered a short biographical questionnaire (only at T1) and three self-report questionnaires at pre (T1), post (T2), and follow-up (T3 and T4) intervention. Children in the IIG will receive the intervention programme before the children in the DIG. It is envisaged that the programme will be delivered to the two groups (the IIG and DIG) of children according to the following outline:

Initial assessment of all children, IIG and DIG (T1)Children in the IIG receive the anxiety intervention programme (5 weeks)Re-assessment of all children, IIG and DIG (T2)Children in the DIG receive the anxiety intervention programme (5 weeks)Re-assessment of all children, IIG and DIG (T3)Final assessment of all children, IIG and DIG (T4 – It will be 6 months after the children in the IIG received the intervention and 3 months after the children in the DIG received the intervention). Resulting from time constraints, where all assessments should be conducted within one academic year, there will be no 6 month follow-up for the DIG, and no wait period for the IIG.

It will be possible to measure:

The stability of the measures when untreated over time (The DIG will act as a wait-list control group using T1 and T2 comparisons)The impact of the anxiety intervention programme immediately after completion (using immediate pre and post-data from both groups – IIG [T1 and T2]; and DIG [T2 and T3])The maintenance of the effects of the anxiety intervention programme over time following intervention (IIG using T2, T3 [3 month] and T4 [6 month] comparisons, and DIG using T3 and T4 [3 month] comparisons)

The following six hypotheses are to be tested during the evaluation phase of the proposed study (four hypotheses pertain to between group effects and two hypotheses pertain to within group effects).

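### As worded, the protocol article applies the Mann-Whitney test, which assumes independent samples, to pre-versus-post differences and names no paired test for its two within-group hypotheses

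*Protocol article*

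**What the plan says.** The protocol article's Statistical analyses section gives the small sample (N = 60) as the reason for a non-parametric approach and then states that "a Mann-Whitney test will be used to determine the significance of differences between the quantitative pre-and-post intervention measures". No other inferential test is named. The following sentence describes two comparisons between the randomised groups: "Pre-intervention (T1) scores will be analysed to determine the equivalence of the IIG and the DIG", and "change scores (difference between the pre-and post-intervention scores) for the IIG and DIG will be compared to evaluate change".

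Programme evaluation counts the hypotheses: "four hypotheses pertain to between group effects and two hypotheses pertain to within group effects". The two within-group hypotheses are "Within the IIG there will be a significant reduction in anxiety scores on the RCADS from T1 to T2" and "Within the DIG there will be a significant reduction in anxiety scores on the RCADS from T2 to T3". The same two reductions are the specific expectations that close the Introduction. Programme evaluation also says that immediate impact will be measured from pre and post data in each group, at T1 and T2 for the IIG and at T2 and T3 for the DIG.

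**The concern.** A pre score and a post score from one child are a correlated pair. The Mann-Whitney test takes its null distribution from two samples of different, independent individuals. Given the T1 scores of 30 children as one sample and the T2 scores of the same 30 as the other, it judges the shift against between-child spread that the pairing would remove. With positive correlation the reference variance is too large, so the p-value is too large.

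At stake are the two hypotheses that the Introduction singles out. A real reduction could be reported as non-significant because of the test chosen. A small sample can justify a rank test. It does not justify an unpaired one, and it makes discarding the pairing more costly.

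**Working it through.** The article gives no power, effect size, SD, significance level or sample-size calculation, so there is no stated figure to reproduce.

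**Inputs from the article**
- Children per group: n = 30 (Method).
- Nearest available correlation: "one-week test-retest correlation coefficients ranging from .65 to .80" (Participant outcomes, for the RCADS scales). This is only a proxy, because each pre-post interval spans a five-week programme. A value of 0.50 was added for that reason.

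**Assumptions**
- Two-sided 5% level, bivariate normal scores, equal SDs and no dropout.
- The true reduction d is in units of the score SD.

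**Step 1: variance.** For means, the true variance of the pre-post difference is 2(1 − ρ)/n in SD² units. An unpaired test in effect uses 2/n. The overstatement is 1/(1 − ρ):
- ρ = 0.50: 1/0.50 = 2.0
- ρ = 0.65: 1/0.35 = 2.86
- ρ = 0.80: 1/0.20 = 5.0

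**Step 2: actual error rate at nominal 5%.** The approximation for means is 2Φ(−1.96/√(1 − ρ)), which gives 0.0056, 0.0009 and 0.00001 at ρ = 0.50, 0.65 and 0.80. Simulating the rank test itself (20,000 runs per cell, n = 30) gives 0.0076, 0.0017 and 0.0002. The last is about 4 rejections in 20,000 runs, so only its order of magnitude should be relied on. The signed-rank test on the same pairs gives 0.0495, 0.0494 and 0.0500.

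**Step 3: power.** The same simulation, Mann-Whitney versus signed-rank:

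| d (SD) | ρ = 0.50 | ρ = 0.65 | ρ = 0.80 | Share of power lost |
|---|---|---|---|---|
| 0.3 | 0.13 v 0.35 | 0.09 v 0.46 | 0.05 v 0.69 | 63-92% |
| 0.4 | 0.26 v 0.55 | 0.24 v 0.69 | 0.19 v 0.90 | 52-79% |
| 0.5 | 0.44 v 0.73 | 0.44 v 0.87 | 0.44 v 0.98 | 40-55% |
| 0.8 | 0.91 v 0.99 | 0.95 v 1.00 | 0.98 v 1.00 | 2-7% |

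Share lost is 1 − (Mann-Whitney power / signed-rank power). For example, at d = 0.3 and ρ = 0.50 it is 1 − 0.1268/0.3458 = 0.63.

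**Step 4: closed-form check** at d = 0.5 and ρ = 0.65.
- Standard error used: √(2/30) = 0.258. True standard error: √(2 × 0.35/30) = 0.153.
- Unpaired power: Φ((0.5 − 1.96 × 0.258)/0.153) = 0.484.
- Paired power: Φ(0.5/0.153 − 1.96) = 0.905.

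The simulated rank tests give 0.44 and 0.87. They are slightly lower, with the same gap.

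**Step 5: between-group use.** Mann-Whitney on change scores, 30 IIG against 30 DIG children, has a simulated error rate of 0.0495, 0.0492 and 0.0495 at the three correlations. That use is sound.

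**The case against.** The strongest reply is that the sentence about Mann-Whitney merely introduces the next one, which lists only comparisons between IIG and DIG. On that reading no wrong p-value arises. The within-group hypotheses just lack a named test, which a condensed article may leave to the full plan. The mention of non-parametric statistics in general does not exclude a paired rank test.

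This reading is possible, but it does not clear the text. The literal wording attaches an unpaired test to pre and post measures, and Programme evaluation defines the pre-post comparison as T1 with T2 in the IIG and T2 with T3 in the DIG. An analyst following the article as written would use the wrong test.

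Other parts of the reply stand and limit the point:
- **Size of the loss.** A reader might infer that most of the power is always lost. The article gives no effect size to support that. The loss is large at 0.3 to 0.4 SD, about half at 0.5 SD and small at 0.8 SD.
- **Correlation.** The one-week test-retest range is not a pre-post correlation in these children, and differing responses to the programme could lower it.
- **Maintenance.** A reader might infer that Mann-Whitney would also hide relapse in the follow-up comparisons. Statistical analyses assigns no test to post-versus-follow-up comparisons, so that would be an extrapolation.
- **Randomised evidence.** A reader might infer that the main treatment comparison is compromised. It is not: the T1 comparison, the change-score comparison and IIG at T2 against DIG at T3 all involve different children.

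**Conclusion.** The point holds within limits. Followed as worded, the article uses an independent-samples test on paired data for two of its six hypotheses, and it names no paired alternative. For pre-post correlations of 0.50 to 0.80 the true error rate falls from 5% to between about 0.8% and 0.02%. The share of power lost runs from 63-92% at 0.3 SD to 2-7% at 0.8 SD. These figures rest on the assumptions listed with the calculation, chiefly normal scores, no dropout and a proxy correlation.

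The error is conservative: it can hide a real within-group reduction but does not raise the rate of false claims of benefit. The randomised comparisons between IIG and DIG are valid uses of Mann-Whitney and are untouched. This is a genuine error of specification that costs almost nothing to correct, and it does not threaten the trial's main contrast.

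**What to change.** In Statistical analyses, restrict Mann-Whitney to comparisons between IIG and DIG. State that the two within-group hypotheses, and any other comparison of the same children at two time points, will use a paired test such as the Wilcoxon signed-rank test. A mixed model across T1 to T4 is an option but is not needed to cure this defect.

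The cost is one sentence, with no new data and no design change.

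Separately, retention at follow-up should not be concluded from a non-significant result alone. Naming a paired test does not cure that weakness.
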